### Statistical considerations

#### Sample size

The sample size calculation is based on the primary objective to compare the silicon nitride and PEEK cages with respect to improvement in RMDQ score and to demonstrate that the silicon nitride cage is non-inferior to the PEEK cage.

In a large spinal fusion cohort study, Robertson [47] found a mean RMDQ improvement of about 10 points. Scheufler also noted an improvement from a pre-treatment score of 17 to 7 at eight months post-op, with a standard deviation of 4 [48]. Both studies included patients with back pain from degenerative disc disease and degenerative spondylolisthesis.

The maximal difference between the treatment arms that could be considered potentially no longer clinically relevant for the RMDQ is thus a difference in improvement of 2–3.5 points [39,41,49]. We therefore consider a non-inferiority margin of 2.6 points between the treatment arms to reflect the maximal difference that is not clinically relevant. Non-inferiority is to be demonstrated based on a one-sided confidence interval with significance level of 2.5% for the difference between the two treatment arms. Assuming a standard deviation of 4 points, 50 patients per arm provide 90% power to demonstrate non-inferiority within a non-inferiority margin of 2.6 points. The total of 100 patients shall be randomized into two groups to minimize bias. This sample size is based on comparing treatment groups with a *t*-test. The actual analysis is a repeated measurements analysis with baseline as covariate, which is more efficient (requiring less patients, at least about 10% if the correlation between baseline and endpoint is 0.3). Thus, no additional sample size increase is incorporated to account for drop-out. Sensitivity analyses to assess impact of drop outs will be performed.

#### Statistical analysis

The primary analysis will be on the change from baseline in RMDQ score. This will be analyzed based on a mixed model for repeated measurements, including baseline RMDQ as covariate and treatment and center as factors. No imputation will be applied for this analysis. The primary comparison will be at 12 months of follow-up.

Sensitivity analyses to assess impact of drop outs will be performed. These will include an analysis based on Last Observation Carried Forward imputation, as well as multiple imputations based on differential patterns of drop out/missing data reasons.

An exploratory analysis of the distribution of the individual improvements in change from baseline in RMDQ score versus the fusion rate (in three categories) within treatment groups will be performed to assess the extent to which both are consistent.

Other continuous outcomes assessed at each visit will be analyzed similarly. Dichotomous outcomes will be compared between treatment groups based on Z-tests for comparing proportions, with results expressed as 95% confidence intervals for the difference in proportions.

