**Methods/Design:**

This study is designed as a double blind multi-center randomized controlled trial with repeated measures analysis. 100 patients (18–75 years) presenting with symptomatic lumbar degenerative disorders unresponsive to at least 6 months of conservative treatment are included. Patients will be randomly assigned to a PEEK cage or a silicon nitride cage, and will undergo a transforaminal lumbar interbody fusion with pedicle screw fixation. Primary outcome measure is the functional improvement measured by the Roland Morris Disability Questionnaire. Secondary outcome parameters are the VAS leg, VAS back, SF-36, Likert scale, neurological outcome and radiographic assessment of fusion. After 1 year the fusion rate will be measured by radiograms and CT. Follow-up will be continued for 2 years. Patients and clinical observers who will perform the follow-up visits will be blinded for type of cage used during follow-up. Analyses of radiograms and CT will be performed independently by two experienced radiologists.

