### Outcome measurements

Several validated questionnaires described below will be used for outcome assessments. During intake, a basic physical exam with neurological examination (muscle strength, reflexes) and additional assessments as required per normal practice will be performed to ensure that the patient can undergo surgery safely. During follow-up visits at 3, 6, 12 and 24 months the neurological examination will be repeated. See Table 2 for the patient follow-up chart.

**Table 2 T2:** Follow-up chart

	**Intake**	**Admission**	**3 months**	**6 months**	**12 months**	**24 months**
Visit	1	2	3	4	5	6
Demography	X					
Study information + informed consent	X					
Randomization	X					
Surgery		X				
Operative data		X				
Neurological examination	X		X	X	X	X
Questionairres:	X		X	X	X	X
- Roland Morris disability questionairre						
- SF-36						
- VAS back						
- VAS leg						
- Working status						
Likert scale		X	X	X	X	X
X-rays	X	X	X	X	X	X
CT					X	
MRI	X					
Complications		X	X	X	X	X

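### Dichotomous outcomes are fixed to an unadjusted Z-test, which is valid but gives up precision that the plan's own adjusted approach to continuous outcomes would recover

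*Protocol article*

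**What the plan says.** The Statistical analysis section of the protocol article gives two rules for comparing the arms.

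- **Continuous outcomes.** Change in RMDQ is analysed by a mixed model "including baseline RMDQ as covariate and treatment and center as factors". The rule is then extended: "Other continuous outcomes assessed at each visit will be analyzed similarly".
- **Dichotomous outcomes.** "Dichotomous outcomes will be compared between treatment groups based on Z-tests for comparing proportions". The form of the result is fixed too: "with results expressed as 95% confidence intervals for the difference in proportions". No covariate is named, and a two-proportion Z-test has no place for one.

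The Sample size section gives the reason for adjusting RMDQ. The baseline-adjusted analysis is called more efficient, needing roughly 10% fewer patients when baseline and endpoint correlate at 0.3.

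The only outcome that the article expressly dichotomizes is the Likert recovery score (Secondary outcome measures). It is first completed at discharge, so it has no intake value. Two other items are recorded at intake and again at 3, 6, 12 and 24 months: "Working status", a questionnaire line in Table 2, and the neurological examination ("During follow-up visits at 3, 6, 12 and 24 months the neurological examination will be repeated"). The article gives neither of them a coding or a cut-off. The abstract lists the secondary outcomes thus: "Secondary outcome parameters are the VAS leg, VAS back, SF-36, Likert scale, neurological outcome and radiographic assessment of fusion". Neurological outcome is in that list; working status is not.

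**The concern.** The plan sets out the efficiency argument for baseline adjustment and applies it to every continuous outcome assessed at each visit. It then drops it for dichotomous outcomes without giving a reason. The same variance argument holds for a difference in proportions when a measured baseline variable predicts the outcome.

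Two things are at stake, both confined to secondary outcomes. First, the confidence interval may be wider than the collected data allow, in a trial of 100 patients with no allowance for drop-out. Second, if the arms differ by chance on a prognostic baseline variable, the crude difference carries part of that imbalance and a reader cannot separate it from a cage effect.

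This is not a detail left to an unseen analysis plan. The article names the method.

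**Working it through.** **Inputs from the article:** 50 per arm, SD 4, margin 2.6, one-sided 2.5%, 90% power, correlation 0.3 for RMDQ (Sample size); Z-test and risk difference with 95% interval (Statistical analysis).

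**Assumed, because the article gives no value:** proportion 0.5 for a dichotomous outcome; correlation rho between that outcome and its baseline covariate of 0.1, 0.3 or 0.5; all 50 patients per arm observed.

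**1. The plan's own figures.**
- n per arm = 2 × (1.960 + 1.282)² × 4² / 2.6² = 49.7, so 50. Power at 50 per arm is Φ(2.6/0.8 − 1.96) = Φ(1.29) = 90.1% (89.6% with the t distribution). The stated size reproduces.
- Gain from adjustment at 0.3: 1 − 0.3² = 0.91, a 9% saving. This agrees with the stated figure of about 10%.

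**2. The same argument for a risk difference.**
- Crude SE = √(2 × 0.5 × 0.5 / 50) = 0.100; half-width = 1.96 × 0.100 = 19.6 points.
- Adjusted half-width = 19.6 × √(1 − rho²); equivalent patients per arm = 50 / (1 − rho²).

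| rho | Variance reduction | 95% CI half-width (points) | Equivalent n per arm |
|---|---|---|---|
| 0 (crude) | 0% | 19.6 | 50 |
| 0.1 | 1% | 19.5 | 51 |
| 0.3 | 9% | 18.7 | 55 |
| 0.5 | 25% | 17.0 | 67 |

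**3. Simulation** (40,000 trials, 50 per arm, no treatment effect, binary baseline covariate with prevalence 0.5, linear adjustment).
- The crude difference averages about 0, so it is unbiased. The Z-test's two-sided type I error is about 5.7%, a small effect of discreteness.
- The SD of the estimate falls from 0.100 to 0.096 (rho 0.3) and to 0.087 (rho 0.5), in line with the table.

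**4. Chance imbalance.**
- The SD of the baseline difference between arms is √(2 × 0.25 / 50) = 10 points. In the simulation, a difference of 10 points or more in either direction arose in about 37% of trials.
- Given a 10-point baseline difference, the expected shift in the crude estimate is about rho × 10 points, that is 3 points (rho 0.3) or 5 points (rho 0.5). The simulation gave 2.6 and 5.1. The adjusted estimate shifted by −0.4 and 0.1, close to zero.

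**5. Limit on rho.** When the covariate is a binary intake value at 50%, its correlation with a follow-up proportion of 75% cannot exceed √(0.25/0.75) = 0.58, and with one of 70% it cannot exceed √(0.30/0.70) = 0.65. The table therefore stops at 0.5.

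The gain from adding center cannot be computed. The article gives no difference in outcome between its two sites.

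**The case against.** The strongest objection is that nothing here is an error. In a randomized trial the crude difference in proportions is unbiased, and its 95% interval already allows for chance imbalance on average. Step 3 bears this out. Choosing an unadjusted analysis for secondary outcomes that did not drive the sample size is an efficiency choice, and no conclusion on the primary endpoint depends on it. All of that stands. A reader might infer that the Z-test produces a biased cage effect, and the article does not support that. The imbalance in step 4 is conditional on an unlucky allocation and averages out over randomizations.

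A reader might also infer that working status and neurological status will be compared by this Z-test while their intake values are ignored. The article does not say so.

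- No dichotomy is defined for either.
- Working status is absent from the list of secondary outcomes in the abstract and is not described under Secondary outcome measures.
- The neurological examination covers muscle strength and reflexes with no cut-off, and the complications section has a category for worsened neurological symptoms that is already relative to an earlier state.

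The two items are examples of where the rule would apply if they were dichotomized, and no more than that.

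Finally, the size rests wholly on an assumed rho. The only correlation in the article is 0.3, for RMDQ, and at that value the gain is modest. Nothing indicates how strongly baseline RMDQ predicts the Likert score. These objections shrink the point. They do not remove it, because the method is stated, the data are already collected, and the plan itself endorses the reason for adjusting.

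**Conclusion.** The point holds as an optional improvement. The article fixes an unadjusted test for dichotomous outcomes while adjusting continuous ones, and so gives up precision and leaves chance baseline imbalance in the estimate. It certainly applies to the dichotomized Likert score, through baseline RMDQ and center. It applies beyond that only to outcomes that are in fact analysed as dichotomous and have an intake value.

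With 50 per arm and a proportion of 0.5, both assumed for the dichotomous outcome, the loss is negligible at rho 0.1 (0.1 point of half-width), small at 0.3 (0.9 point) and material at 0.5 (2.6 points, the equivalent of about 17 patients per arm). The crude test remains valid, and the primary RMDQ comparison is untouched.

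**What to change.** In the Statistical analysis section, replace the Z-test sentence with a covariate-adjusted risk difference and its 95% confidence interval:

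- Fit a logistic regression with treatment, center and the outcome's own intake value where one exists. For the dichotomized Likert score, use baseline RMDQ in place of the intake value.
- Standardise the fitted model to a difference in proportions, which keeps the effect measure that the plan already uses.
- Report the unadjusted proportions beside it.
- Prespecify a minimum event count below which the unadjusted difference is used, so that the choice of analysis is not made after seeing the results.

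The cost is one sentence and a little programming, with no new data, visits or patients. The small downside is that a model-based estimate is slightly harder to explain and needs the sparse-event rule.

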Silicon nitride (Si_3_N_4_) is a ceramic with a compression strength exceeding the usual plastic and metal materials used for interbody cages. Unlike many other ceramics, silicon nitride resists brittle fractures; its toughness exceeds that of alumina, a material with 30+ years of use in joint replacements [27]. Silicon nitride is also highly compatible with standard imaging techniques. The material is free from artifacts on radiogram, CT and MRI images [26]. Several studies have demonstrated its biocompatibility and its mechanical and osteoconductive qualities in vitro [28-32]. Furthermore, compared to PEEK and titanium, silicon nitride has a decreased bacterial activity on its surface [33,34]. Based on good results in vitro, silicon nitride is used in the development of bearings that can improve wear and longevity of knee and hip prosthesis [32].

A preliminary study with silicon nitride interbody cages showed good clinical and radiological results in 2 patients 1 year after a transforaminal lumbar interbody fusion procedure [35]. Sorrell et al. presented the results of a 10 year clinical follow-up study [36]. In this study 30 patients underwent anterior interbody fusion of the lumbar spine using silicon nitride cages. They found a durable interbody fusion after 5 years (21 out of 22 patients) and after 10 years (16 out of 16 patients). Please note there was a 47% loss of follow-up. Silicon nitride materials received the CE Mark and FDA market clearance for its use as interbody cages in 2008. They have been used in the US for over 3 years, with no adverse events reported [32].

Compared to PEEK cages silicon nitride cages are expected to have lower complications rates and allow higher fusion rates due to better biocompatible and osteoconductive qualities. The purpose of this study is to compare the clinical outcomes and fusion rates of PEEK cages with silicon nitride cages in patients with symptomatic degenerative lumbar disc disorders.

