### Complications, adverse events, additional surgery

The investigators will record all complications and adverse events accurately. These will be grouped in the following categories:

● Infections, grouped as superficial wound infections and deep wound infections

● Post-surgical hematoma

● Increased neurological symptoms

● Venous thrombosis

● Other (serious) adverse events

All adverse events and complications will be monitored and followed up until stable or resolved during the course of the study. Each adverse event will be reported to the operating surgeon and will be associated to the type of cage used to qualify the event to be related. Code breaking will occur by the clinical observer or operating surgeon if the clinical condition of the patient necessitates this*.* Early termination of the study will be decided if necessary.

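### Z-tests with 95% intervals are set for every dichotomous outcome with no exception for sparse counts; if the simple Z interval is used at 50 per arm, it can be too narrow or even zero-width for rare events

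*Protocol article*

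**What the plan says.** The Statistical analysis section of the protocol article gives a single rule for binary outcomes: "Dichotomous outcomes will be compared between treatment groups based on Z-tests for comparing proportions". The same sentence asks for 95% confidence intervals for the difference. It names no interval formula and has no alternative for small counts.

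Three other places show where the rule may be applied:

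- **Complications, adverse events, additional surgery** groups events by type. One line reads "Infections, grouped as superficial wound infections and deep wound infections"; the others are hematoma, increased neurological symptoms, venous thrombosis and other adverse events. No expected rates are given.
- **Secondary outcome measures** dichotomizes the Likert recovery score, again without an expected rate. It is the only outcome that the article explicitly splits in two.
- **Background** reports earlier fusion results with silicon nitride: "They found a durable interbody fusion after 5 years (21 out of 22 patients", followed by 16 of 16 at ten years. It also cites a 14.3% subsidence rate with PEEK cages.

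The trial size comes from the RMDQ: "50 patients per arm provide 90% power to demonstrate non-inferiority within a non-inferiority margin of 2.6 points".

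**The concern.** A Z method for a difference in proportions relies on a normal approximation with a standard error estimated from the observed proportions. When an arm has no events, that arm's estimated variance is zero. When it has one or two, the variance is poorly estimated and often too small. With 50 patients per arm and complications divided by type, cells with zero or few events are plausible.

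The article expects the new cage to give fewer complications and more fusion. Unequal rates close to 0% or 100% would therefore be in line with its own hypothesis, and that is where the simple interval performs worst. At stake is the reporting of safety and fusion for a new implant: an interval that is too short, or has no width, suggests more certainty than 50 patients per arm can supply.

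**Working it through.** **The plan's own figure.** Inputs from the Sample size section: margin 2.6 points, SD 4 points, one-sided 2.5%, power 90%.

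n per arm = 2 × 4² × (1.960 + 1.282)² / 2.6² = 49.7, so 50. Power at 50: 2.6 / (4 × √(2/50)) = 3.25; 3.25 − 1.96 = 1.29, which gives 90.1% (89.6% with the noncentral t). The stated size reproduces. The article states no coverage figure or expected rate for the dichotomous outcomes, so the rates below are assumptions.

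**Formulas**, with p₁ and p₂ the observed proportions and n = 50 per arm:

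- Simple Z (Wald): p₁ − p₂ ± 1.96 × √[p₁(1 − p₁)/n + p₂(1 − p₂)/n].
- Newcombe: Wilson limits (lᵢ, uᵢ) for each arm. Lower limit p₁ − p₂ − √[(p₁ − l₁)² + (u₂ − p₂)²]; upper limit p₁ − p₂ + √[(u₁ − p₁)² + (p₂ − l₂)²].
- Coverage: the summed binomial probability of all tables whose interval contains the true difference (exact enumeration).

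**Coverage at 50 per arm**

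| True rates | Simple Z | Newcombe |
|---|---|---|
| 1% vs 3% | 78.0% | 99.7% |
| 2% vs 4% | 86.4% | 99.2% |
| 1% vs 5% (or 99% vs 95%) | 91.3% | 99.1% |
| 98% vs 90% | 93.3% | 97.5% |
| 5% vs 14.3% | 94.3% | 96.7% |
| 10% vs 14.3% | 94.3% | 96.1% |

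Using the pooled standard error instead changes little: 78.0%, 86.4% and 91.8% in the first three rows.

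**Why the first row is so low.** The true difference is −2 points. Three tables account for nearly all of the shortfall:

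- 0 vs 0 events: probability (0.99 × 0.97)⁵⁰ = 13.2%. The interval is 0 to 0 and misses.
- 1 vs 0: probability 0.3056 × 0.2181 = 6.7%. The lower limit is 0.02 − 1.96 × √(0.02 × 0.98/50) = −1.9 points, a narrow miss.
- 2 vs 0: probability 0.0756 × 0.2181 = 1.6%. The lower limit is 0.04 − 1.96 × √(0.04 × 0.96/50) = −1.4 points, a miss.

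Together these make 21.5 of the 22.0 points of non-coverage.

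**Where the problem is absent.** With equal rates the simple interval covers 99.8% at 1%, 98.7% at 2%, 94.6% at 5% and 94.3% at 14.3%. Its minimum over equal rates from 0.5% to 50% is 93.9%. On a grid with both rates between 10% and 90% the minimum is 93.1% and the mean 94.3%.

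**Two concrete tables**

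- 0/50 vs 0/50: the simple interval is 0 to 0, and the Z statistic is 0/0 and cannot be computed. The Wilson upper limit in each arm is 7.1%, so Newcombe gives −7.1 to +7.1 points. If both true rates are 1%, this table occurs with probability 0.99¹⁰⁰ = 37%.
- 0/50 vs 4/50: the simple interval is −0.08 ± 1.96 × √(0.08 × 0.92/50), or −15.5 to −0.5 points, which excludes zero. The pooled Z is −0.08 / √(0.04 × 0.96 × 2/50) = −2.04. Newcombe gives −18.8 to +0.6 and Fisher's exact p is 0.12; neither reaches significance.

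The second table separates the methods, but not all score methods fall on the same side. At a difference of zero, the Miettinen-Nurminen statistic is the pooled Z times √(99/100), here 2.04 × 0.995 = 2.03. That exceeds 1.96, so this interval also excludes zero.

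**The case against.** The strongest reply is that the article fixes a test, not an interval. A score interval inverts a Z statistic, so Miettinen-Nurminen already fits the wording, and score coverage stayed at about 94% or more in every case checked. The choice of interval and the handling of sparse tables could properly sit in an analysis plan that is not shown. This stands in part: a reader might infer that the Wald interval is prescribed, and the text does not say so. What remains is that the sentence covers all dichotomous outcomes without exception, and the simple interval is the natural reading beside a Z-test.

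A reader might also infer that the Z-test inflates false positives. It does not do so materially: its exact size is 0.2% when both rates are 1%, 1.3% when both are 2%, and never above 5.7%.

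Nor does the article show that its dichotomous outcomes lie near 0% or 100%. Likert recovery has no stated rate. The fusion figures come from anterior fusion at five and ten years in a 30-patient series, for which the Background itself notes 47% loss to follow-up; they do not forecast transforaminal fusion at one year. The exploratory analysis treats fusion in three categories, so a binary fusion comparison is an inference. So is a separate between-arm test for each complication type. The only complication rate cited, 14.3% subsidence, lies where the simple interval works.

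Finally, a 0 to 0 interval is easy to recognize beside the counts. That is fair for this one table, but less so for intervals that are merely too short.

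**Conclusion.** The point holds in a limited form. The sentence applies Z-tests to every dichotomous outcome and has no provision for sparse counts. If the simple Z interval is used, nominal 95% intervals can cover as little as about 78% to 91% in the extreme and unequal scenarios listed, and the interval degenerates when neither arm has an event. These sizes rest on two assumptions: that the interval is of the simple type, and that the rates, which the article does not give, are as low (or for fusion as high) as supposed. Without both, coverage is about 94% or better and there is little to correct.

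The 0/50 vs 4/50 table shows that the conclusion can depend on the method; it does not by itself show which method is right.

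The reach is confined to individual complications, and to fusion if it is dichotomized. The primary RMDQ comparison uses a mixed model and is unaffected. Severity is minor: a cheap improvement, not a flaw that threatens the trial's main conclusion.

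**What to change.** Add one sentence to the Statistical analysis section: differences in proportions will be reported with score-type 95% intervals, either Newcombe or Miettinen-Nurminen, and an exact test will be used for sparse tables. Name one interval in advance and define sparse, because the two intervals can disagree at the edge, as at 0/50 vs 4/50, where Newcombe agrees with Fisher's exact test and Miettinen-Nurminen with the Z-test.

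The methods are in standard software and need no new data or patients. The cost is slightly wider intervals for rare events, for example −13.5 to +3.7 points (Newcombe) instead of −9.4 to +1.4 (simple Z) at 0/50 vs 2/50.
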